#### Analysis of secondary outcomes

Secondary outcomes will be compared in the intention-to-treat cohort only. Categorical outcomes will be compared in the intention-to-treat using a chi-square test. Results will be reported as RR with 95% CI. Continuous outcomes will be compared using generalized linear mixed models. Results will be reported as beta estimates with 95% CI.

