#### Secondary outcomes

A detailed list of secondary outcomes with definitions has already been published and is outlined in Supplement Table S4. These secondary outcomes can be grouped as follows:
Mortality outcomes
ICU mortalityHospital mortalityEndotracheal intubation. We will document time to intubation, reasons for intubation as determined by the treating team (neurologic deterioration that is not attributed to sedation, persistent or worsening respiratory failure of NIV such as SaO2 < 88%, respiratory rate > 36/min, PaO_2_:FiO_2_ ratio < 100 or persistent requirement of FiO_2_ ≥ 70%, intolerance of mask or helmet NIV, airway bleeding, copious respiratory secretions, respiratory acidosis with pH < 7.25, hemodynamic instability, or significant radiological worsening). We will document mechanical ventilation parameters in the first 24 h after intubation (peak airway pressure, plateau pressure, PEEP in cm H_2_O), FiO_2_, tidal volume, and respiratory rate. We will also document oxygen rescue therapies during invasive mechanical ventilation (neuromuscular blocker infusion, recruitment maneuvers, inhaled nitric oxide, prone positioning, extracorporeal membrane oxygenation (ECMO)). We will report the percentage of patients who underwent tracheostomy.Continuous outcomes
ICU-free days at day 28Hospital length of stay (LOS)Invasive mechanical ventilation-free days at day 28Renal replacement therapy-free days at day 28Vasopressor-free days at day 28Safety outcomes
Skin injury at the nose, face, neck, and axillae, with the highest stage during the intervention period. We will use the stages as per the National Pressure Ulcer Advisory Panel [14]: stage I: non-blanchable erythema, stage II: partial thickness, stage III: full-thickness skin loss, and stage IV: full-thickness tissue lossBarotrauma, including pneumothorax, mediastinal air or subcutaneous emphysemaCardiovascular eventsDevice complications (such as helmet deflation or malfunction)Serious adverse events (SAEs)Follow-up study: There will be a follow-up of enrolled patients at day 180 about vital status, functional status (EuroQoL (EQ)-5D-5L), by an unblinded assessor, which is planned to be reported separately. For patients who have been discharged from the hospital before day 180, follow-up will be conducted by telephone.

We will also report protocol violations (Supplement Table S6).

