### Statistical analysis

Details of sample size calculation have already been published in the study protocol [11]. The sample size of 320 provides a power of 80% to detect a 15% absolute risk reduction in 28-day mortality from 40 to 25%. Categorical variables will be reported as numbers and frequencies and will be compared between the study groups using the chi-square test or Fisher’s exact test. Continuous variables will be reported as means and standard deviations or medians and the first and third quartiles (Q1–Q3) and will be compared between the study groups using the Student’s *t*-test or the Wilcoxon–Mann–Whitney test, as judged appropriate by normality testing using Shapiro–Wilk test. For serial measurements (such as SaO_2_:FiO2 ratio, fluid balance, and serial SOFA), we will test the change over time and the difference between the two study groups over time using generalized linear mixed effect models by considering the link function of logit to incorporate the binary nature of the response variable and link function of log for score outcomes, with no imputation for missing values. To adjust for multiple testing for secondary outcomes and subgroup analyses, we will use the false discovery rate (FDR) as described by Benjamini and Hochberg [15]. We will report associations as relative risk (RR) or hazard ratio (HR) with 95% confidence intervals (CI) or beta coefficient and 95% CI as appropriate. We will compare dyspnea scores and device discomfort scores using generalized linear mixed models, incorporating fixed effects of treatment, time, and the treatment by time interaction and random effects of patient and center. Tests will be two-sided and at the 5% significance level. All statistical analyses will be conducted using the SAS software version 9.4 (SAS Institute, Cary, NC, USA). The statistical analysis remains blinded to the research team until completion of primary outcome data on the study population and will be performed by the study biostatistician. A summary of the analysis plan is provided in Table 1.

**Table 1 Tab1:** Summary of the analysis plan

Variables	Intention-to-treat cohort	Per-protocol cohort
Baseline characteristics	No statistical comparisons	None
Intervention and co-interventions	Chi-square, Fisher’s exact test, Wilcoxon–Mann–Whitney test, *t*-test as applicable	None

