#### Interim analyses

The interim test statistics will be conducted for the primary outcome. Two formal interim analyses are planned when 33% and 67% of the sample size are reached. The trial may be stopped for safety (*p* < 0.01) or effectiveness (*p* < 0.001) both evaluating the primary outcome (28-day mortality) but there will be no plans to terminate the trial for futility. We will account for alpha spending by the O’Brien-Fleming method and the final *p*-value will be considered at 0.048 [20].

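### Raw hospital length of stay is compared over all randomized patients with no stated handling of deaths, so a survival benefit would appear as a longer stay

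*SAP article*

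**What the plan says.** The section *Secondary outcomes* lists five continuous outcomes. Four are counts of free days at day 28 (ICU, invasive ventilation, renal replacement therapy, vasopressors). The fifth is hospital LOS, given as a plain duration.

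The section *Analysis of secondary outcomes* sets the cohort, "Secondary outcomes will be compared in the intention-to-treat cohort only", and the method, "Continuous outcomes will be compared using generalized linear mixed models", with a beta estimate and 95% confidence interval. Table 1 names the same method for continuous secondary outcomes. The intention-to-treat population is all randomized patients, apart from narrow post-randomization exclusions that do not concern death, so LOS is not limited to survivors. *Statistical analysis* adds that secondary outcomes are tested with a false discovery rate adjustment, so LOS is a tested comparison and not only a description.

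Nothing in the article says how a patient who dies in hospital enters the LOS comparison. On definitions it says: "A detailed list of secondary outcomes with definitions has already been published and is outlined in Supplement Table S4".

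Intubation is binary and falls under a different sentence: "Categorical outcomes will be compared in the intention-to-treat using a chi-square test".

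**The concern.** Hospital stay ends in one of two ways, live discharge or death, and a raw duration does not distinguish them. A short stay is good if the patient went home and the worst result if the patient died. A model of raw LOS over all randomized patients gives both the same value, so the beta mixes survival with speed of recovery.

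This would matter little if deaths were rare. Here the plan expects a quarter to two fifths of patients to die within 28 days, and it expects the arms to differ in exactly that respect. If the trial succeeds on its primary outcome, the LOS comparison is pushed against the helmet by the benefit itself. A reader could then take a longer mean stay as a cost in recovery or resource use per survivor when it only reflects patients who lived long enough to have a longer stay.

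**Working it through.** **The plan's own figure.** The only design figure is: "The sample size of 320 provides a power of 80% to detect a 15% absolute risk reduction in 28-day mortality from 40 to 25" (per cent). With 160 per arm (1:1 allocation), d = 0.40 − 0.25 = 0.15 and pooled risk 0.325:

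- standard error under the null = √(2 × 0.325 × 0.675 / 160) = 0.0524
- standard error under the alternative = √((0.40 × 0.60 + 0.25 × 0.75) / 160) = 0.0517
- power = Φ((0.15 − z × 0.0524) / 0.0517)

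This gives 82.0% at two-sided 5% and 81.6% at the final level of 0.048; a continuity correction at 5% gives 78.7%. The stated 80% is consistent with these, so the mortality rates of 40% and 25% can be used as the plan's own inputs.

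**Effect of deaths on mean LOS.** Let m be the arm's mortality, S the mean stay of survivors and D the mean stay of those who die. Then

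arm mean = (1 − m) × S + m × D.

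To isolate the artefact, S and D are the same in both arms, so the helmet has no effect on survivors' stay. Helmet minus usual care is

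(0.40 − 0.25) × (S − D) = 0.15 × (S − D).

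The documents give neither S nor D; the values below are assumptions. The 28-day mortality stands in for death during the hospital stay.

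| S (days) | D (days) | Gap | Helmet mean | Usual care mean | Difference |
|---|---|---|---|---|---|
| 20 | 14 | 6 | 18.50 | 17.60 | +0.90 |
| 20 | 10 | 10 | 17.50 | 16.00 | +1.50 |
| 20 | 7 | 13 | 16.75 | 14.80 | +1.95 |
| 25 | 10 | 15 | 21.25 | 19.00 | +2.25 |
| 20 | 20 | 0 | 20.00 | 20.00 | 0.00 |

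An 8-day gap gives 0.15 × 8 = +1.2 days. The artefact vanishes if survivors and decedents stay equally long on average, or if mortality is the same in both arms.

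**The same case scored as hospital-free days.** Suppose every survivor stays 20 days and deaths score 0. Survivors then have 28 − 20 = 8 free days. The arm means are 0.75 × 8 = 6.0 (helmet) and 0.60 × 8 = 4.8 (usual care), a difference of +1.2 free days in favour of the helmet. The mortality effect is still in the measure, but it now has the right sign.

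**Intubation, checked for the same fault.** Let f be the share of deaths that were never intubated and s the intubation risk in survivors (both assumed). Intubation risk = m × (1 − f) + (1 − m) × s.

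- Same f in both arms, mortality 40% v 25%, s = 20%: the relative risk is 0.400/0.520 = 0.769 at f = 0, 0.375/0.480 = 0.781 at f = 10% and 0.325/0.400 = 0.813 at f = 30%. It moves toward 1, not in the helmet's favour.
- Different f, equal mortality of 32.5%, s = 25%: with f = 20% (helmet) v 5% (usual care), the risks are 0.325 × 0.80 + 0.675 × 0.25 = 0.429 and 0.325 × 0.95 + 0.675 × 0.25 = 0.478, relative risk 0.90. Intubation or death is 0.325 + 0.675 × 0.25 = 0.494 in both arms, relative risk 1.00.

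**The case against.** The strongest objection is that outcome definitions are placed elsewhere. Supplement Table S4 or the protocol may restrict LOS to survivors, assign deaths a value, or report LOS by vital status. This stands as a limit on the claim: it can be said only that the article states no handling of death, not that the trial has none. It does not remove the point, because the article itself fixes both the cohort and the method, and a survivors-only or death-ranked LOS would need to be stated there.

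A second objection is that LOS is one unranked secondary outcome, reported beside 28-day, ICU and hospital mortality and four free-days outcomes, so a careful reader could see a survival-driven shift. That is fair and limits the weight of the point. A beta with a confidence interval and an adjusted p-value will still be read on its own, though, and none of the free-days outcomes covers hospital stay.

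A reader might also infer that intubation is mishandled in the same way, since a patient who dies un-intubated counts as not intubated. The documents do not support this. With complete follow-up, a proportion at a fixed horizon, with deaths kept in the denominator, already equals the cumulative incidence of intubation with death as a competing event. The error would arise if deaths were censored in a Kaplan–Meier estimate, and the article specifies Kaplan–Meier and Cox methods for mortality only. For intubation timing it says only: "We will document time to intubation, reasons for intubation as determined by the treating team". Nor would un-intubated deaths by themselves make the helmet look better; that needs their share to differ between arms, and the documents give no figure for it. What remains is a matter of interpretation: in an unblinded trial where the treating team determines the reasons for intubation, such a difference is possible.

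**Conclusion.** The point holds for hospital LOS, on the article's text. As written, the comparison counts an early death as a short stay, and at the planned mortality effect it shifts mean LOS against the helmet by 0.15 × (survivor stay minus decedent stay): 1.2 days for an assumed 8-day gap and 2.25 days for an assumed 15-day gap, with recovery unchanged.

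The size rests on the plan's 40% and 25%, on an assumed gap, and on stays within survivors and within decedents being the same in both arms. If decedents stayed longer than survivors, the sign would reverse. A smaller mortality difference shrinks the shift in proportion.

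The primary analysis is unaffected. The chi-square comparison of intubation is a valid comparison of how often patients are intubated, and it is not part of the fault.

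**What to change.** Before the database is locked, replace the tested LOS comparison with one of two measures and name it in *Analysis of secondary outcomes* and Table 1:

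- time from randomization to live discharge, with death as a competing event (cumulative incidence by arm, Fine–Gray model for the comparison); or
- hospital-free days at day 28, with deaths scored 0, in line with the free-days outcomes already listed.

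Keep raw LOS as a descriptive figure by vital status and arm, without a test. A tested survivors-only comparison is not a good substitute, because survival is itself affected by treatment. If Supplement Table S4 or the protocol already has a rule for deaths, carry it into the article's text and check it against the intention-to-treat statement.

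The cost is one extra analysis, from discharge and death dates that a trial reporting LOS and hospital mortality should already hold. Both measures include the mortality effect, so neither is a pure measure of duration; the text should say so.

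Optionally, report intubation or death by day 28 as a relative risk beside the intubation result. This costs one table row and would show whether un-intubated deaths differ between arms. The intubation test itself stays as planned.

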#### Subgroup analyses

The primary outcome will be compared in the intention-to-treat cohort only, in the following a priori defined subgroups using a chi-square test.
PaO_2_:FiO_2_ ratio 101–200 and PaO_2_:FiO_2_ ratio < 100Obese patients (body mass index > 30 kg/m^2^) and patients with a body mass index of ≤ 30 kg/m^2^Patients aged > 65 years and ≤ 65 yearsAPACHE II score higher or lower than the median of enrolled patientsPatients who were at the time of enrollment on mask NIV versus other types of respiratory support

Results will be reported using RR and 95% CI. We will report the results of the test of interactions for these subgroups (Supplement Table S5).

#### Sensitivity analyses

We will compare the primary outcome between the helmet NIV and usual care groups in the per-protocol cohorts (effectiveness analysis). If patients with suspected COVID-19 who tested negative constituted more than 5% of the study population, we will carry a sensitivity analysis excluding these patients.

#### 180-day follow-up study

In a follow-up report, we will compare 180-day mortality and the EuroQol (EQ-5D-5L) [17] at 6-month scores after randomization between the two study groups. The EQ-5D-5L scores will be converted into a single index value that generates a measure of utility ranging from −0.111 to 1.000 (1.000 indicates full health) using an online tool [18, 19]. We will use generalized linear mixed models to compare EQ-5D-5L index values and VAS scores between the two groups by incorporating treatment, baseline values, and random patient and center effects in the model.

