### Study population

All adult (adult ICU cut-off age) patients admitted to the ICU with suspected or confirmed COVID-19 by reverse transcription-polymerase chain reaction (RT-PCR) will be screened for eligibility. Inclusion criteria include acute hypoxemic respiratory failure (PaO_2_:FiO_2_ ratio < 200 despite supplemental oxygen with a partial/non-rebreathing mask at a flow rate of 10 L/min or above) with intact airway protective gag reflex and ability to follow instructions. Exclusion criteria include imminent intubation and the requirement for more than one vasopressor. A full list of inclusion and exclusion criteria is described in the published protocol [11]. Enrolled patients will be randomized using a concealed online system to helmet NIV with usual care or usual care alone at a 1:1 ratio. Usual care may include mask NIV, HFNO, or standard oxygen therapy. Randomization will be stratified by site. Helmet NIV will be delivered in pressure support mode, with initial settings of pressure support of 8–10 cm H_2_O, PEEP of 10 cm H_2_O with FiO_2_ of 100%, targeting flow rate of ≥ 50 L/min with an inspiratory rise time of 50 ms, and end flow/cycling off of 50% of maximal inspiratory flow. The settings can be adjusted according to the study protocol. The management of respiratory support in the usual care group including mask NIV is at the discretion of the treating team.

A flow diagram will be constructed according to the CONSORT guidelines (Fig. 1). We will report the number of patients who were screened, met inclusion or exclusion criteria, and were eligible but not enrolled with reasons for non-enrollment. We will report the number of patients who were randomized to each group, received the allocated intervention, withdrawn/lost-to-follow-up with reasons, and included in the final analysis.

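### The day-180 EQ-5D-5L and VAS comparison is labelled intention-to-treat but, as written, covers survivors only, so it is not a randomised comparison

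*SAP article*

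**What the plan says.** The Secondary outcomes section of the SAP article plans the assessment: "There will be a follow-up of enrolled patients at day 180 about vital status, functional status (EuroQoL (EQ)-5D-5L" by an unblinded assessor, to be reported separately. The 180-day follow-up study section converts the questionnaire to an index, "a measure of utility ranging from −0.111 to 1.000 (1.000 indicates full health". It then sets the analysis: "We will use generalized linear mixed models to compare EQ-5D-5L index values and VAS scores between the two groups", with terms for treatment and baseline value and random effects for patient and centre. Mortality at 180 days is compared in the same section by its own test.

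Table 1 lists the EQ-5D-5L and VAS models in both the intention-to-treat and per-protocol columns. The Study population section defines the intention-to-treat population as every randomised patient, apart from narrow post-randomisation exclusions.

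The article gives no score to patients who have died, does not restrict the comparison to survivors in words, and plans no analysis that combines survival with quality of life. The only limitation that the Discussion names for quality of life is the lack of blinding.

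**The concern.** A patient who has died has no questionnaire. With no score assigned, the model can use only patients alive at day 180. Survival is what the helmet is meant to change, and deaths are expected to be common: the Statistical analysis section plans for "80% to detect a 15% absolute risk reduction in 28-day mortality from 40 to 25" per cent. If the helmet works, its survivors include patients with no counterpart among the usual-care survivors, so the two groups being compared are no longer the randomised groups.

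A mixed model does not repair this, because a score after death is undefined rather than missing at random. At stake is the reading of a separate follow-up report: a beta estimate with a confidence interval, labelled intention-to-treat, would be taken as the effect of randomisation on quality of life.

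**Working it through.** **Design figures.** The article states: "The sample size of 320 provides a power of 80% to detect a 15% absolute risk reduction in 28-day mortality from 40 to 25" per cent. Allocation is to helmet or "usual care alone at a 1:1 ratio", so 160 per arm; "Tests will be two-sided and at the 5% significance level".

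n per arm = [1.960 × √(2 × 0.325 × 0.675) + 0.842 × √(0.40 × 0.60 + 0.25 × 0.75)]² / 0.15² = 151.9, so 152 per arm and 304 in total. With 160 per arm the power is 82.0% at 0.05. It is 81.6% at the final level in the Interim analyses section ("value will be considered at 0.048"). The stated 80% is reproduced closely enough to take 40% and 25% as the design rates.

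**Who can be scored.** Assume that the day-28 rates persist to day 180 and that no patient dies because of the helmet.

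- Usual care: 160 × 0.60 = 96 survivors. Helmet: 160 × 0.75 = 120 survivors.
- Alive in either arm (always-survivors): 60%. Alive only with the helmet (saved): 15%. Dead in either arm: 25%.
- Saved share of helmet survivors: 0.15 / 0.75 = 20%.
- For assumed 180-day rates of 40/30, 45/30 and 50/35: 0.10/0.70 = 14%, 0.15/0.70 = 21% and 0.15/0.65 = 23%.

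**Shift in the survivor contrast.** Let u be the mean index of always-survivors under usual care, g their true gain on the helmet, and d how far the saved patients score below u. The article gives none of these.

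Survivor difference = [0.60(u + g) + 0.15(u − d)] / 0.75 − u = 0.8g − 0.2d.

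This is zero at g = 0.25d; a smaller true gain appears as a loss.

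All-randomised difference with death scored 0 = 0.60(u + g) + 0.15(u − d) − 0.60u = 0.60g + 0.15(u − d).

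| d | Survivors only, g = 0 | Largest gain hidden or reversed (0.25d) | All randomised, g = 0, u = 0.70 | All randomised, g = 0, u = 0.80 |
|---|---|---|---|---|
| 0.1 | −0.02 | 0.025 | +0.090 | +0.105 |
| 0.2 | −0.04 | 0.050 | +0.075 | +0.090 |
| 0.3 | −0.06 | 0.075 | +0.060 | +0.075 |
| 0.4 | −0.08 | 0.100 | +0.045 | +0.060 |

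For VAS, assumed gaps of 10 to 30 points shift the survivor contrast by −0.2 × 10 = −2 to −0.2 × 30 = −6 points.

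**With a true gain.** At g = 0.03 the survivor difference is 0.024 − 0.02 = +0.004 for d = 0.1, and 0.024 − 0.04 = −0.016 for d = 0.2. Reversal therefore depends on the inputs.

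**Against sampling error.** With an assumed SD of 0.25, SE = 0.25 × √(1/96 + 1/120) = 0.034. At g = 0 the estimate favours usual care with probability 72% (d = 0.1) to 99% (d = 0.4). It does so significantly with probability 8% to 65%.

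**The case against.** The strongest reply is that the defect is read from silence in a condensed article. Outcome definitions are referred to a supplement table and to the published protocol, neither of which is shown, and either may say how deaths are handled. That caution stands as far as it goes. But the article does not leave this analysis to another document: it names the endpoints, the model, its terms and the cohort. Followed as written, they give a survivor contrast under an intention-to-treat label.

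A reader might also infer that, if the helmet saves lives, its quality-of-life result will come out in the wrong direction. The documents do not support that, for three reasons.

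- The opposite signs in the table are built in. Any d above 0 with g = 0 makes the survivor difference negative, and any positive utility in saved patients makes the other difference positive. Nothing in the article shows that saved patients score lower.
- The two differences answer different questions. With g = 0 the all-randomised figure is 0.15 × (u − d), the mortality difference weighted by utility. It is not the true value that the survivor figure misses.
- A benefit in always-survivors offsets the shift, as the g = 0.03 case shows.

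Two further points reduce the weight. 180-day mortality is reported beside the scores, so a reader will see any survival difference. Baseline adjustment may narrow severity differences between the survivor groups. Neither makes the contrast a randomised one.

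**Conclusion.** The point holds as one of labelling and estimand. The day-180 index and VAS comparison, as specified, is conditional on survival while carried as intention-to-treat. On the design rates a fifth of helmet survivors (14% to 23% over the other rates tried) have no counterpart in the usual-care survivors. The contrast is shifted by −0.2 × d, which is −0.02 to −0.08 index points for d of 0.1 to 0.4, and a true gain of up to 0.25 × d could be hidden or reversed.

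This rests on the day-28 gap lasting to day 180, on no survival harm from the helmet, and on assumed values of d. The composition problem follows from the design rates. The size and sign of the bias do not, and a reversed result is possible rather than expected. The outcome is secondary and separately reported, and the 28-day mortality conclusion is untouched. It should be corrected before day-180 results are seen.

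**What to change.** In the 180-day follow-up study section and in Table 1:

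1. Label the mixed-model comparisons of index and VAS as among survivors, and state that they carry no causal claim.
2. Prespecify beside them an all-randomised comparison of mean index. Patients known to have died by day 180 are scored 0, declared as a convention because the article anchors only full health. Adjust for centre and give a robust or bootstrap 95% CI.
3. Show both next to 180-day mortality.

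VAS has no comparable anchor for death in the article, so it stays descriptive among survivors. If the protocol or supplement already has a rule for deaths, cite it here.

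The cost is SAP wording and about one line of code, since vital status at day 180 is already collected. The downside is that the all-randomised figure mixes survival with quality of life. For that reason it is added to the survivor results rather than replacing them.
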